## **2.17 Results dissemination**

Study findings will be communicated to participants, the community, and pertinent stakeholders in time. Clear and comprehensible information about the results, their implications will be provided and any recommendations for practice will be provided if necessary

## 2.18 Permissions and Ethical clearance

This study obtained necessary permission and ethical clearance from the College Education Department, letter no. **DCEHRH- 2023-24/423** Government of Sindh, Pakistan, and applied for ethical approval from the local Institutional Review Committee of the Mekran Medical College, for ethical clearance. Written informed consent from study participants will be acquired.

### Appendix I. Study Gantt Chart

[figure not shown]

### Appendix II. Sample size calculations

Phase II(CRCT)

To determine a significant association between the respondent’s characteristics, knowledge, beliefs, and practices on breast self-examination among college teachers.

Sample size calculation will be done by applying formula two proportion/two sample for t testing hypothesis and observing expected differences in proportions of BSE practice between two groups.

n = [(Z_ı - α)√(2P̅(1 - P̅)) + (Z_ı - β)√(Pı(1 - Pı) + P2(1 - P2))] / (Pı - P2)²

Table 3.3: Information of sample size derivation

| **Attribute** | **Assumptions** |
| --- | --- |
| **Z** | Cluster Randomized Controlled Trial |
| **Z(1-α)** | Zα= 1.96; p-value= 0.05; therefore, power desired is 0.95 |
| **Z(1−β)** | Zβ=0.84; β=0.20; 0.80 power was desired. (James 2001) |
| **P1** | P1=85.6% Prevalence of regular breast self-examination practice in intervention group 06 months post intervention(ABDULRAHMAN, 2020) |
| **P2** | P2=26%, Prevalence of regular breast self-examination practice in control group 06 months post intervention(ABDULRAHMAN, 2020) |

Sample size n= **14** calculated by openEpi(Charan & Biswas, 2013) 2 groups 14* 2 = 28

28 x [1 + (m-1) ICC)

Where: m=average cluster size,

ICC-class correlation coefficient m

ICC =0.02: intra-cluster correlation coefficient based on Cluster randomised controlled trial comparing the effectiveness and cost-effectiveness of two primary care interventions aimed at improving attendance for breast screening (Richards et al., 2001),

m= 99 (average cluster size calculated)

n​=28×[1+(m−1) ×ICC]

Given that average cluster size =99

ICC=0.02:

n=28× [1+(99−1) ×0.02]

n=28× [1+98×0.02]

n=28× [1+1.96]

n=28×2.96

n≈82.88

Rounding up to the nearest whole number, the final adjusted sample size without considering attrition and eligibility adjustments would be approximately 83.

To adjust for a 20% attrition rate, we need to increase the sample size by dividing it by the complement of the attrition rate, which is 1-0.2 = 0.8. So:

83 / 0.8 = 103

To adjust for the eligibility proportion of 90%, we need to further increase the sample size by dividing it by the eligibility proportion. So:

103 / 0.9 = 114

The final required sample size with attrition and eligibility adjustments is approximately 114 teachers.

114/2 =57

57 participants in each group.

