| **Eligibility Criteria** | A. Inclusion criteria  For colleges  Willing to be a part of the study.  • For teachers  • Full-time faculty appointed in government colleges in Hyderabad district.  • Aged between 25-59 years.  • Willing to be part of the study.  B. Exclusion criteria  • For colleges  • Colleges that are not willing to participate in the study despite meeting the inclusion criteria.  • Colleges already participated in initial phases of study, pilot testing, and cross-sectional study.  • For Teachers  • Pregnant teachers and lactating mothers  • Those who are on sabbatical leave.  • Diagnosed/Recovered breast cancer patients.  • Teachers who will refuse to be part of the study |
| **Sample size** | 114 for both arms, 57 in each arm. |
| **Intervention** | Health belief theory-based breast self-examination intervention delivered to the intervention group |
| **Control Group** | Will receive the intervention at the end of the study |
| **Data Collection Points** | Baseline, post-intervention at two different time points, 1 month and 3 months. |
| **Primary Outcome** | Practice and frequency associated with breast self-examination |
| **Secondary Outcome** | Knowledge of breast cancer and breast self-examination, beliefs linked with breast cancer and breast self-examination |
| **Discussion** | This cluster randomized controlled trial aims to improve the efficacy and legitimacy of theory-based breast self-examination interventions by increasing women's knowledge of the need for breast cancer awareness and changing their attitudes to encourage early breast cancer detection. |

| Chief Investigator &Main supervisor | [name] [name] |
| --- | --- |
| Co-Investigator &Co-supervisor | [name] |
| Co-Investigator | [name] |

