**Step 2:**

**Randomize Within Blocks:**

- Each block will be randomly assigned to one of the treatment groups. For example, flip a coin or use a random number generator to determine whether Block 1 goes to the intervention or control group, and similarly for Block 2.

**Required sample size:** The Total sample size required for the second phase of study is 114, that is 57 participants in each arm.

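### Appendix II truncates both loss adjustments: on the plan's own inputs the total sample size is 116 (58 per arm), not 114

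*Combined protocol and SAP*

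**What the plan says.** Appendix II takes its two proportions from a cited earlier study: "P1=85.6% Prevalence of regular breast self-examination practice in intervention group 06 months post intervention" and "P2=26%, Prevalence of regular breast self-examination practice in control group 06 months post intervention". For power it states "Zβ=0.84; β=0.20; 0.80 power was desired". This leads to 14 teachers per arm: "2 groups 14* 2 = 28".

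The 28 is multiplied by a design effect using an ICC of 0.02 and a cluster size given as "m= 99 (average cluster size calculated". The product, 82.88, is explicitly rounded up to 83. The plan then divides by 0.8 for attrition and reports 103, and divides that by 0.9 for eligibility and reports 114.

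The result is used throughout. The Study Summary has "114 for both arms, 57 in each arm". Section 2.7, Step 2 has "The Total sample size required for the second phase of study is 114, that is 57 participants in each arm". Section 2.6 repeats it, and Section 2.7, Steps 3 and 4 divide the 57 per arm into whole-number quotas by college and faculty.

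**The concern.** Appendix II changes its rounding rule partway through. It rounds 82.88 up, then drops 0.75 from one quotient and 0.44 from the next. Entering 103.75 as 103 is neither rounding up nor rounding to nearest. The purpose of the two divisions is to make the invited number large enough that the required 83 remain after losses, and truncating works against that purpose.

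At stake is the correctness of a figure that appears in four places and sets every college quota. A reader who repeats the divisions will not obtain 114.

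**Working it through.** **Inputs, all from Appendix II unless stated.** Unadjusted total 28; ICC 0.02; m = 99; attrition 20%, so retention 0.8; eligibility 0.9. College rolls from Section 2.7, Step 1: 112, 88, 117 and 81.

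**Reproducing the plan's figure.**
- Design effect: 1 + (99 − 1) x 0.02 = 2.96.
- 28 x 2.96 = 82.88, rounded up to 83.
- 83/0.8 = 103.75; the plan carries 103.
- 103/0.9 = 114.44; the plan carries 114, or 57 per arm.

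The printed 114 arises only if 103.75 is cut to 103 before the last division.

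**The same chain with consistent rounding.**

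| Rule | After design effect | After attrition | After eligibility |
| --- | --- | --- | --- |
| Round up at each step | 83 | 104 | 104/0.9 = 115.56, so 116 |
| Round to nearest at each step | 83 | 104 | 115.56, so 116 |
| Round up once, from 83 | 83 | – | 83/0.72 = 115.3, so 116 |
| Round up once, from 82.88 | 82.88 | – | 82.88/0.72 = 115.1, so 116 |

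Here 0.72 = 0.8 x 0.9.

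**Reverse check, counting invited teachers.**
- 114 x 0.72 = 82.08, below 82.88 and 83.
- 115 x 0.72 = 82.80, still below 82.88.
- 116 x 0.72 = 83.52, which is enough.

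So 116 is the smallest total that meets the plan's requirement, and it splits evenly into 58 per arm.

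**Effect on power.** With the plan's design effect, 82.08 evaluable teachers correspond to 82.08/2.96/2 = 13.86 effective teachers per arm, and 83 correspond to 14.02. For 85.6% against 26%, two-sided 0.05, without continuity correction, power is 93.3% and 93.6% respectively.

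**Cluster size, a separate slip.** (112 + 88 + 117 + 81)/4 = 398/4 = 99.5, not 99. The design effect becomes 1 + 98.5 x 0.02 = 2.97, and 28 x 2.97 = 83.16. One final rounding gives 83.16/0.72 = 115.5, so 116 again. Rounding up at every step gives 84, 105 and 117.

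**College quotas at 58 per arm.** A: 112/200 x 58 = 32.48, so 32. B: 88/200 x 58 = 25.52, so 26. C: 117/198 x 58 = 34.27, so 34. D: 81/198 x 58 = 23.73, so 24. Each arm sums to 58. The present quotas show similar inconsistency: at 57 per arm, A is 31.92 and is listed as 31, while B is 25.08 and is listed as 26.

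**The case against.** **The consequence is negligible.** The plan calls both 83 and 114 approximate. The gap is under one teacher at analysis. The base of 14 per arm is also generous: recomputing it gives 10 without and 13 with continuity correction, and with 13 the requirement would be 26 x 2.96 = 76.96, which 82.08 exceeds. This stands, and it fixes the point as minor. It does not make the quotients right, because the plan goes on to use 114 as an exact number for arms and quotas.

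**The 82 depends on what 114 counts.** Sections 2.6 and 2.7 describe the 57 per arm as participants. If they are already eligible and enrolled, 114 x 0.8 = 91.2 remain, above 83. The wording leaves this open. Two things favour the invited reading: dividing by 0.9 makes sense only for a count taken before eligibility screening, and Section 2.7, Step 5 selects and invites teachers before eligible ones consent. The analysis section also carries forward the last record of dropouts, so 82 is the number retained under the plan's attrition figure and not necessarily the number analysed. The quotients are wrong on either reading.

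**A larger question sits in the same step.** The 99 is a whole-college roll, whereas about 114/4 = 28.5 teachers per college are sampled. With m = 28.5 the design effect is 1.55, and rounding up at each step gives 44, 55 and 62. The choice of m therefore outweighs the rounding. That is a reason to apply one rounding rule to whichever chain is finally used, not a reason to leave the present one uncorrected.

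**Conclusion.** The point holds as a minor arithmetic correction. From 28, a design effect of 2.96, 20% attrition and 90% eligibility, the total is 116 (58 per arm), not 114. If 114 counts teachers invited before screening, it yields about 82.1 evaluable teachers against the 83 required: a shortfall of 0.92 of a teacher, or two invitations.

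A reader might infer three stronger things that the documents do not support:
- That the trial is underpowered because of this. Power moves by about 0.3 points and, on the plan's assumptions, stays well above 80%.
- That taking 99 instead of 99.5 causes the shortfall. The 83 already rests on m = 99, m = 99 already leads to 116, and m = 99.5 with one final rounding gives 116 as well.
- That the total must be 117, or 118 for equal arms. Those figures need m = 99.5 together with rounding up at every intermediate step, a convention the plan does not lay down.

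The conclusion takes the plan's 28, ICC and loss rates as given. It does not judge those inputs or the number of clusters.

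**What to change.** Correct the two quotients in Appendix II (103.75 to 104; 115.56 to 116) and restate the total as 116, 58 per arm, in the Study Summary, Sections 2.6 and 2.7, and Appendix II. Recompute the college quotas as A 32, B 26, C 34 and D 24, and let the faculty quotas follow by one stated rounding rule. Alternatively, keep 114 and state that it yields about 82 evaluable teachers. In either case, say whether the figure counts teachers invited or participants enrolled.

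Give the average roll as 99.5 if the whole-college size is kept. If the design effect is recalculated with the number sampled per college, apply the same rounding rule to the new chain.

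The cost is a text edit plus two more invitations from a frame of 398 teachers, or one added sentence if 114 is kept.

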**SECTION II: KNOWLEDGE**

**2.1 KNOWLEDGE OF BREAST CANCER RISK FACTOR**

|  |  | YES | NO | I DON’T KNOW | Rating |
| --- | --- | --- | --- | --- | --- |
| BCRF1 | Being obese or having dense breast tissue is a known risk factor for breast cancer. |  |  |  |  |
| BCRF 2 | The risk of breast cancer increases with age. |  |  |  |  |
| BCRF 3 | A family history of breast cancer elevates the chances of developing breast cancer. |  |  |  |  |
| BCRF 4 | Abnormal genes inherited from parents can increase the risk of breast cancer. |  |  |  |  |
| BCRF 5 | A personal history of benign(noncancerous)diseases increases the chances of breast cancer. |  |  |  |  |
| BCRF 6 | First childbirth at a later age after 30 increases the likelihood of developing breast cancer. |  |  |  |  |
| BCRF 7 | Prolonged breastfeeding for one year or more may lower the risk of breast cancer in women. |  |  |  |  |
| BCRF 8 | Delivering to several children more than five or six reduces the chances of breast cancer |  |  |  |  |
| BCRF 9 | Taking birth control pills and hormones increases the risk of breast cancer. |  |  |  |  |
| BCRF 10 | After menopause, being obese increases the risk of breast cancer. |  |  |  |  |
| BCRF 11 | The late onset of menopause after 55 is associated with a higher risk of breast cancer. |  |  |  |  |
| BCRF 12 | Early menarche increases the risk of breast cancer. |  |  |  |  |
| BCRF 13 | Does radiation therapy in the chest area increase the chances of breast cancer? |  |  |  |  |

**2.2 KNOWLEDGE OF BREAST CANCER SYMPTOMS**

|  |  | YES | NO | I don’t know | Rating |
| --- | --- | --- | --- | --- | --- |
| BCS1 | Are changes in the size or shape of the breast considered possible symptoms of breast cancer? |  |  |  |  |
| BCS2 | Is nipple discharge, other than breast milk, a potential symptom of breast cancer? |  |  |  |  |
| BCS3 | Are changes in the skin texture of the breast, such as redness or dimpling, indicative of breast cancer symptoms? |  |  |  |  |
| BCS4 | A painless lump in the breast is a sign of breast cancer. |  |  |  |  |
| BCS5 | Do breast cancer symptoms sometimes include unexplained pain or tenderness in the breast? |  |  |  |  |
| BCS6 | Are persistent breast or nipple itching a potential symptom of breast cancer? |  |  |  |  |
| BCS7 | Swelling and pain in the armpit region is a sign of breast cancer. |  |  |  |  |
| BCS8 | Change in shape and size of the nipple is a sign of breast cancer. |  |  |  |  |

**2.3 KNOWLEDGE OF BREAST CANCER SCREENING**

|  |  | YES | NO | I don’t know | Rating |
| --- | --- | --- | --- | --- | --- |
| BCS1 | Are you aware of different breast cancer screening methods like breast self-examination, clinical breast examination or mammography? |  |  |  |  |
| BCS2 | Early detection is the only way to get effective treatment? |  |  |  |  |
| BCS3 | A breast examination by a healthcare provider is an important step in the early detection of breast cancer |  |  |  |  |
| BCS4 | Mammography can identify breast cancer in its early stages. |  |  |  |  |

**2.4 KNOWLEDGE OF BREAST SELF EXAMINATION**

|  |  | Yes | No | I don’t know | Rating |
| --- | --- | --- | --- | --- | --- |
| BSE1 | Breast self-examination is a way for women to become aware of their breasts. |  |  |  |  |
| BSE2 | The right age to begin practicing breast self-examination is 20 years of age. |  |  |  |  |
| BSE3 | Breast self-examination can be performed while standing and lying down on the bed. |  |  |  |  |
| BSE4 | Breast self-examination should be performed once after period of three months. |  |  |  |  |
| BSE5 | The best time to perform breast self-examination is after the 7^th^ day of the menstrual cycle. |  |  |  |  |
| BSE6 | While performing breast self-examination during the shower, the individual should raise one arm and gently move the fingers on every part of the breast. |  |  |  |  |
| BSE7 | Menopausal women can perform breast self-examination at a particular date every month. |  |  |  |  |
| BSE8 | Both breasts should be examined in the same way to notice any change. |  |  |  |  |
| BSE9 | During breast self-examination, you should check for any skin thickening or lump in the breast. |  |  |  |  |
| BSE 10 | Breast self-examination should involve checking for lumps in the underarm region. |  |  |  |  |
| BSE11 | Performing breast self-examination while lying down, fingers flat press gently in small circles starting from the topmost corner of the breast. |  |  |  |  |

**SECTION III- BELIEFS (HBM scale)**

This section contained closed-ended questions which will be measure using a 5-point Likert scale statements ranging from (5) strongly disagree (4) disagree, (3) not sure, (2) agree, (1) strongly agree. Respectively.

|  |  | Strongly Agree | Agree | Neutral | Disagree | Strongly disagree |
| --- | --- | --- | --- | --- | --- | --- |
| SBC 1 | It is extremely likely I will get breast cancer in the future. |  |  |  |  |  |
| SBC2 | I feel I will get breast cancer in the future. |  |  |  |  |  |
| SBC3 | There is a good possibility I will get breast cancer in the next 10 years. |  |  |  |  |  |
| SBC4 | My chances of getting breast cancer are higher. |  |  |  |  |  |
| SBC5 | I am more likely than the average woman to get breast cancer. |  |  |  |  |  |

**3.1 SUSCEPTIBILITY OF BREAST CANCER**

**3.2 SERIOUSNESS OF BREAST CANCER**

|  |  | Strongly Agree | Agree | Neutral | Disagree | Strongly disagree |
| --- | --- | --- | --- | --- | --- | --- |
| SNBC 1 | The thought of breast cancer scares me. |  |  |  |  |  |
| SNBC 2 | When I think of breast cancer my heart beats faster. |  |  |  |  |  |
| SNBC 3 | I am afraid to think about breast cancer. |  |  |  |  |  |
| SNBC 4 | Problems I would experience with breast cancer would last a long time. |  |  |  |  |  |
| SNBC 5 | Breast cancer would threaten my relationship with my husband. |  |  |  |  |  |
| SNBC 6 | If I had breast cancer my whole life would change. |  |  |  |  |  |
| SNBC7 | If I developed breast cancer, I would not live longer than 5 years. |  |  |  |  |  |

**3.3 BENEFITS OF BSE**

| BBSE 1 | When I do breast self-examination, I feel good about myself. | Strongly agree | Agree | Neutral | Disagree | Strongly disagree |
| --- | --- | --- | --- | --- | --- | --- |
| BBSE 2 | When I complete monthly breast self-examination, I don’t worry as much about breast cancer. |  |  |  |  |  |
| BBSE 3 | Completing breast self-examination each month will allow me to find lumps early. |  |  |  |  |  |
| BBSE 4 | If I complete breast self-examination monthly during the next year, I will decrease my chance of dying from breast cancer. |  |  |  |  |  |
| BBSE 5 | If I complete breast self-examination monthly, I will decrease my chance of requiring radical or disfiguring surgery if breast cancer occurs. |  |  |  |  |  |
| BBSE 6 | If I complete monthly breast self-examination, it will help me to find a lump, which might be cancer before it is detected by a doctor or nurse. |  |  |  |  |  |

**3.4 BARRIERS OF BSE**

|  |  | Strongly agree | Agree | Neutral | Disagree | Strongly  disagree |
| --- | --- | --- | --- | --- | --- | --- |
| BRBSE 1 | I feel funny doing breast self-examination. |  |  |  |  |  |
| BRBSE 2 | Doing a breast self-examination during the next year will make me worry about breast cancer. |  |  |  |  |  |
| BRBSE 3 | Breast self-examination will be embarrassing to me. |  |  |  |  |  |
| BRBSE5 | Doing breast self-examination will be unpleasant. |  |  |  |  |  |
| BRBSE 6 | I don’t have enough privacy to do breast self-examination. |  |  |  |  |  |

**3.5 CONFIDENCE TO PERFORM BSE**

|  |  | Strongly agree | Agree | Neutral | Disagree | Strongly disagree |
| --- | --- | --- | --- | --- | --- | --- |
| CBSE 1 | I know how to perform breast self-examination. |  |  |  |  |  |
| CBSE 2 | I am confident I can perform breast self-examination correctly. |  |  |  |  |  |
| CBSE 3 | If I were to develop breast cancer, I would be able to find a lump by performing breast self-examination |  |  |  |  |  |
| CBSE 4 | I can find a breast lump if I  practice breast self-examination alone. |  |  |  |  |  |
| CBSE 5 | I can find a breast lump the size of a 5-cent coin. |  |  |  |  |  |
| CBSE 6 | I can find a breast lump the size of a 10-cent coin. |  |  |  |  |  |
| CBSE 7 | I can find a breast lump that is the size of a pea. |  |  |  |  |  |
| CBSE 8 | I am sure of the steps to follow for doing a breast self-examination. |  |  |  |  |  |
| CBSE 9 | I can identify normal and abnormal breast tissue when I do breast self-examination. |  |  |  |  |  |
| CBSE 10 | When looking in the mirror, I can recognize abnormal changes in my breast. |  |  |  |  |  |
| CBSE 11 | I can use the correct part of my fingers when I examine my breasts. |  |  |  |  |  |

**3.6 MOTIVATION**

|  |  | Strongly agree | Agree | Neutral | Disagree | Strongly disagree |
| --- | --- | --- | --- | --- | --- | --- |
| M1 | I want to discover health problems early. |  |  |  |  |  |
| M2 | Maintaining good health is extremely important to me. |  |  |  |  |  |
|  |  |  |  |  |  |  |
| M3 | I search for new information to improve my health. |  |  |  |  |  |
| M4 | I feel it is important to carry out activities to improve my health. |  |  |  |  |  |
| M5 | I eat well-balanced meals. |  |  |  |  |  |
| M6 | I exercise at least 3 times a week. |  |  |  |  |  |
| M7 | I have regular health check-ups even when I am not sick. |  |  |  |  |  |

**SECTION IV: PRACTICE**

**BSE Practice**

1. Do you practice BSE regularly to check for any changes or abnormalities in your breasts?

- Yes
- No

2. Which best describes the frequency of your Breast Self-Examinations (BSE)?

- Never
- Once in a month
- Once in a three-month period.
- Once in a six-month period.
